### Adverse event reporting and program oversight

Grade 1 adverse events will be reported to the corresponding medical oncologist for participant evaluation. In the event of any adverse event classified as Grade 2–5, it will be reported to the designated medical oncologists, the Cancer Committee, and the Institutional Review Board (IRB) of the Ethics Committee at Universidad San Francisco de Quito (Quito, Ecuador) for further evaluation and to determine the continuity of the program.

The social worker, together with the principal investigator, will be responsible for monitoring and reporting any potential adverse events to the medical oncologists and the IRB/Ethics Committee, should they arise during the investigation. The oversight of the data and communication among the team members will be the responsibility of the data manager to ensure proper data collection, ethical data sharing and quality control procedures for data entry.

The physical activity program will be conducted at Hospital SOLCA Quito, with support from the physical activity team, as well as a brigade of nurses and emergency room physicians who will be available to provide immediate assistance in the event of any adverse incidents during the program.

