## Material and methods

### Design

This study is designed as a randomized controlled trial to investigate the impact of a structured exercise program on the HRQoL of pediatric cancer patients. A total of 90 participants will be recruited and randomly assigned to either the intervention group or the control group.

The intervention group will participate in a 10-week structured physical activity program consisting of 120 min of supervised exercise per week, led by a team of physiotherapists and physical activity professionals from Hospital Sociedad de Lucha Contra el Cáncer del Ecuador (SOLCA) Quito. Meanwhile, the control group will not participate in any organized physical activity program but will continue with their usual activities. As part of the evaluation process, two versions of the Pediatric Quality of Life Inventory (PedsQL) survey will be administered: one tailored for children aged 8–12 and another for adolescents aged 13–18. Both groups will complete their respective surveys at three time points—baseline (week 0), post intervention (week 11), and follow-up (week 24). This approach allows for the assessment of changes in HRQoL over time and enables comparative analysis between the two age groups.

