### Statistical analysis

The data from the PedsQL surveys will first undergo descriptive analysis by age group surveys for children and adolescents. Numerical variables will be summarized as mean and standard deviation for variables with a normal distribution or median and interquartile range for non-normally distributed variables. Categorical variables will be summarized as absolute and relative frequencies. This descriptive approach will provide an overview of the data and support subsequent analyses (see Supplementary Table 2 for details on variables and survey items).

To evaluate the primary research question regarding the impact of the physical activity program on HRQoL, a bivariate analysis will be conducted. The analysis will compare exposure to the physical activity program (intervention vs. control group) and the PedsQL survey scores at different time points (week 0, week 11, and week 24). For numerical variables with a normal distribution, the Student's t-test for independent samples will be used. For non-normally distributed variables, the Mann–Whitney *U* test will be applied. Additionally, to evaluate within-group changes over time (e.g., baseline vs. end of study), paired tests will be conducted using either the paired Student's t-test for normally distributed variables or the Wilcoxon signed-rank test for non-normally distributed variables.

An intention-to-treat analysis will be employed to ensure the robustness of the results and account for potential non-compliance or missing data. This approach will analyze participants based on their initial group assignment (intervention or control), regardless of adherence to the program or completion of all study components (22).

Statistical significance will be set at *p*-value < 0.05. All analyses will be performed using R Studio (R Project version 4.3.2).

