### Patient recruitment

Patients will be recruited from Hospital SOLCA Quito and Hospital Pediátrico Baca Ortiz. These two hospitals account for approximately 65% of level 3 care and treatment services in the city of Quito, with most of their patients coming from the public health sector. The remaining services are divided among other institutions: approximately 15% are provided by private healthcare facilities, while the final 20% are distributed among several public hospitals that individually account for less than 7% of level 3 care (18).

Recruitment will involve the distribution of a flyer (Figure 1) summarizing the project and inviting potential participants and their legal representatives to learn more. The flyer will also be shared digitally via mobile devices, allowing parents or guardians to review the project details at their convenience.

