### Eligibility and randomization

This study will include participants aged 8–18 years. For study purposes, age groups will be categorized as follows:
•Children: Aged 8–12 years.•Adolescents: Aged 13–18 years (14).Participants will be randomized into one of two groups:
1.Intervention Group: Participates in a structured physical activity program.2.Control Group: Does not participate in the physical activity program.Randomization will be conducted using the REDCap randomization tool with allocation concealment ensured by restricting access to the randomization sequence (15). Medical oncologists involved in recruitment will not have access to group assignments at the time of enrollment. Additionally, the medical oncologist will be blinded for the group assignments, the social worker would know the group assignments for organization in participants for the physical activity program and surveys administered.

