## Limitations

This study acknowledges several limitations. First, budgetary constraints prevented the recruitment of the originally calculated sample size, potentially reducing the statistical power to detect small effect sizes. Second, the study was limited to participants residing in Quito, which excluded a substantial number of eligible patients from other provinces. Third, requiring participants or their families to have access to a cell phone may introduce selection bias and limit the generalizability of findings to lower socioeconomic groups. Fourth, given the nature of the intervention and the primary outcome measure (self-reported HRQoL), blinding of participants and outcome assessors was not feasible, which may increase the risk of response and measurement bias. However, data analysis will be conducted by a researcher not involved in intervention delivery to minimize this risk. Fifth, although intervention adherence will be monitored through attendance logs and fidelity ensured through a structured protocol, individual differences in participation may still influence results. Lastly, since the study was conducted in only two hospitals in Quito, the external validity of the findings may be restricted. Future studies should consider multi-site designs and additional monitoring strategies to improve generalizability and internal validity.

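### The programme runs at only one of the two recruiting hospitals, yet the planned between-arm test leaves hospital out: a minor loss of precision, and no planned look at attendance by hospital

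*Protocol article*

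**What the plan says.** The Patient recruitment section states: "Patients will be recruited from Hospital SOLCA Quito and Hospital Pediátrico Baca Ortiz". Oncologists at both sites enrol the children and record their baseline data (Collection of demographic data, Collection of clinical data), so recruiting hospital is known for each child before allocation.

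The intervention has a single venue. The section on adverse event reporting and oversight says "The physical activity program will be conducted at Hospital SOLCA Quito", and the Design section says that it is "led by a team of physiotherapists and physical activity professionals from Hospital Sociedad de Lucha Contra el Cáncer del Ecuador (SOLCA) Quito". It lasts 10 weeks at 120 supervised minutes per week.

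For the primary question, the Statistical analysis section says that "a bivariate analysis will be conducted" of arm against PedsQL score. Where scores are normally distributed, "the Student's t-test for independent samples will be used"; otherwise the Mann–Whitney test applies. No covariate is named. The analysis is by intention to treat, "regardless of adherence to the program or completion of all study components".

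On allocation, the Eligibility and randomization section says: "Randomization will be conducted using the REDCap randomization tool with allocation concealment ensured by restricting access to the randomization sequence". It does not mention strata or blocks. The Limitations section adds that "intervention adherence will be monitored through attendance logs".

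**The concern.** A SOLCA patient allocated to the programme exercises at the hospital that already looks after them. A Baca Ortiz patient goes to a different hospital. Recruiting hospital is therefore a plausible influence on attendance, and it may also carry differences in case mix that bear on HRQoL. It is recorded before allocation, yet the stated test does not use it.

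Two things are at stake. The first is precision. If mean HRQoL differs between the hospitals, a test that ignores hospital carries that variation as noise, in a trial already cut from 106 per group to about 45. The second is what the pilot can teach. The Discussion offers the results as a basis for larger multicentre trials and mentions feasibility. Whether attendance holds up among patients from a hospital that does not host the programme is a natural feasibility question, and the article plans no breakdown that would answer it.

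**Working it through.** **Inputs from the protocol article (Sample size calculation).** Difference 4.36; SD 11.26; 95% confidence (taken as two-sided α = 0.05); power 80%; 1:1 ratio; 20% loss; final sample 90, about 45 per arm.

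**Assumptions, because the article gives no figure.** Share of children from one hospital: 50–80% for chance imbalance, 50–70% for power. Mean HRQoL difference between hospitals, g: 0–8 points. For dilution, Baca Ortiz share b: 30–50%; fraction of those children not attending, f: 25–50%.

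**1. The article's own figure.** n = 2 × (1.960 + 0.842)² × (11.26/4.36)² ≈ 104.7, so 105 per group by the normal approximation. The t-based solution is 105.67, so 106, as stated. 106/0.80 = 132.5, so 133, as stated. (The formula printed beside the SD gives 15 × √0.15 = 5.81 rather than 11.26. That is a separate matter; 11.26 is used here because it reproduces the stated 106.)

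**2. Chance imbalance in hospital.** For 90 children split 45:45 without stratification, the exact hypergeometric distribution gives:

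| Share from one hospital | SD of difference in share | P(difference ≥ 10 points) | P(difference ≥ 20 points) |
|---|---|---|---|
| 50% | 10.6 points | 39.9% | 9.1% |
| 60% | 10.4 points | 28.2% | 5.2% |
| 70% | 9.7 points | 35.8% | 6.5% |
| 80% | 8.5 points | 18.7% | 1.6% |

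The probabilities do not fall smoothly because the counts are whole numbers. An imbalance d shifts the observed treatment difference by d × g. For g = 5, 10 points of imbalance shift it by 0.5 and 20 points by 1.0. The standard error of the difference is 11.26 × √(2/45) = 2.37.

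**3. Type I error.** The unadjusted t-test was simulated under no treatment effect: 40,000 runs, 54 of 90 children from one hospital, unstratified 45:45 allocation. Rejection rates were 5.0%, 5.1% and 5.0% for g = 0, 5 and 8.

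**4. Precision.** With 11.26 as the total SD and share s from one hospital, the within-hospital SD is √(11.26² − s(1 − s)g²). For s = 0.5 and g = 8 this is √(126.79 − 16) = 10.53, so hospital explains 16/126.79 = 12.6% of the variance. Power (normal approximation; the single degree of freedom is ignored) is Φ(4.36/(SD × √(2/n)) − 1.96):

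| g (points) | 45 per arm, s = 0.5 | 45 per arm, s = 0.7 | 36 per arm, s = 0.5 | 36 per arm, s = 0.7 |
|---|---|---|---|---|
| 0 (same as unadjusted) | 45.1% | 45.1% | 37.6% | 37.6% |
| 3 | 45.7% | 45.6% | 38.1% | 38.0% |
| 5 | 47.0% | 46.7% | 39.2% | 38.9% |
| 8 | 50.2% | 49.3% | 42.0% | 41.2% |

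The 36 per arm is 45 × 0.80, after the stated loss.

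**5. Dilution by non-attendance.** If a fraction f of Baca Ortiz children do not attend and gain nothing, the intention-to-treat effect is 4.36 × (1 − b × f). With b = 0.3 and f = 0.25 it is 4.03 (power 40% at 45 per arm). With b = 0.5 and f = 0.5 it is 3.27 (power 28%). Neither a stratum nor a hospital term alters this.

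**The case against.** The strongest case on the other side has four parts.

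*The article shows no difference in access.* A reader might infer that recruiting hospital determines who can use the programme. The text does not support that. All participants must live within Quito, everyone allocated to the programme may attend, and recent inpatients are excluded, so SOLCA children also travel from home. What stands is that attendance may plausibly differ by hospital, not that it does.

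*Silence on strata is not an unstratified design.* A reader might also conclude that the randomisation is unstratified. The article says neither yes nor no, and a condensed article may leave strata to the full protocol or the REDCap set-up. This objection stands, so no fault is claimed in the allocation. It does not reach the analysis, where the unadjusted test is stated outright. Even if REDCap does stratify by hospital, that test would ignore the stratum.

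*The harm is small and rests on assumed inputs.* This stands. No hospital difference in HRQoL is documented, and the top of the power range needs 8 points, nearly twice the 4.36-point target. Chance imbalance under concealed allocation is not bias.

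*Attendance by hospital can be tabulated at any time from the logs, and listing such tables is commonly left to an analysis plan.* This also stands in part. The data will exist, and the Limitations section concedes that uneven participation may matter. The request is only that the breakdown be named, because it serves the pilot's stated feasibility interest.

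**Conclusion.** The point holds as a minor improvement to a valid method. The documents establish two recruiting hospitals, one venue and a stated between-arm test without hospital. They do not establish bias, an inflated error rate or restricted access.

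The loss is modest. At 45 per arm, power is about 45% without hospital and 45–50% with it. At 36 per arm it is about 38% against 38–42%. Both ranges assume a hospital difference of 0–8 points, 50–70% of children from one hospital and the article's SD of 11.26. If the hospitals do not differ, nothing is gained.

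The larger possible effect is dilution, from 4.36 to between 4.03 and 3.27 under the attendance assumptions above. It is conjectural, and adjustment would not cure it. A table of attendance by hospital would only make it visible.

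**What to change.** In the Statistical analysis section, replace the unadjusted between-arm test with a linear model of PedsQL score on arm, with recruiting hospital as a fixed factor. Report attendance from the existing logs, and the estimated effect, separately by hospital. Keep both descriptive, without subgroup p-values. The subgroups will be small: at an assumed 30% from Baca Ortiz there are 27 children, about 13.5 per arm, and the standard error of their effect is 11.26 × √(2/13.5) = 4.3, about as large as the target difference.

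In the Eligibility and randomization section, state whether REDCap stratifies by hospital. If it does not and allocation has not begun, add hospital as a stratum. If allocation has begun, leave it and rely on the model.

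The cost is one degree of freedom, one short table and possibly one more stratum.

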### Sample size calculation

The sample size calculation for this study was conducted considering a confidence level of 95%, a power of 80%, equal variances between groups, and a 1:1 ratio between sample sizes. The difference in means to be detected was set at 4.36, based on literature identifying this value as the minimum clinically significant difference (17). The common standard deviation was calculated at 11.26, using the formula for the standard error of measurement (SEM = 15 × √1−0.85), where the Cronbach's alpha reliability coefficient is 0.85. The formula for hypothesis testing by comparing means of independent groups was applied using the Epidat 4.2 program, resulting in a required sample size of 106 participants per group. To account for an estimated 20% loss to follow-up, the sample size was increased to 133 participants per group. However, due to budgetary limitations, the final study sample will consist of a total of 90 participants (approximately 45 per group). While this is lower than the 160 participants initially estimated through power calculations, this adaptation reflects real-world constraints commonly encountered in resource-limited settings. The study is therefore best positioned as a pilot randomized controlled trial, with the aim of generating preliminary data to inform future larger-scale interventions.

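### The planning SD of 11.26 is not the result of the formula given for it, which yields 5.81, and no sourced between-child SD is documented

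*Protocol article*

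**What the plan says.** Everything relevant stands in one paragraph of the protocol article, under Sample size calculation. The design settings are given as "considering a confidence level of 95%, a power of 80%, equal variances between groups, and a 1:1 ratio between sample sizes". The effect is introduced with "The difference in means to be detected was set at 4.36, based on literature identifying this value as the minimum clinically significant difference". For the variability the article says: "The common standard deviation was calculated at 11.26, using the formula for the standard error of measurement". It then prints the SEM as 15 times the square root of 1 − 0.85, "where the Cronbach's alpha reliability coefficient is 0.85".

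From these inputs it reports a calculation "resulting in a required sample size of 106 participants per group". It continues: "To account for an estimated 20% loss to follow-up, the sample size was increased to 133 participants per group". The number actually to be enrolled is then set by budget at 90 in total, about 45 per group, and the study is described as a pilot.

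The article gives no source for the 15, reports no observed SD of PedsQL scores, and does not show how 11.26 arises. (The same paragraph mentions 160 as the initial estimate, which does not agree with 106 or 133 per group. That is a separate matter.)

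**The concern.** Two things do not fit. First, a formula is printed together with its supposed result, and the two disagree by a factor of nearly two. Second, the formula is for the wrong kind of quantity. An SEM describes the error in one child's score, while a two-sample comparison of means needs the spread of scores between children within a group.

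The SD is the only input that links the target difference to the required size, so both the 106/133 and any statement of how far 90 falls short depend on it. The Limitations section describes the shortfall as a possible loss of power for small effects. How large that loss is at the article's own minimum important difference cannot be judged without knowing where the SD comes from. The study is also meant to inform larger trials, whose planners may reuse this figure.

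**Working it through.** **Inputs**, all from Sample size calculation: difference Δ = 4.36, stated SD = 11.26, reliability r = 0.85, the number 15 in the SD position of the SEM formula, power 80%, 1:1 allocation, 20% loss, 45 per group actually planned. The 95% confidence level is read as two-sided α = 0.05. Sidedness is not stated, but a one-sided test would give 83 per group and does not match.

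**1. The article's own sample size reproduces.** With n per group = 2 × [(1.96 + 0.84) × SD/Δ]², using unrounded normal quantiles:
- SD 11.26, Δ 4.36: n = 104.7, so 105 by the normal approximation.
- The exact calculation with the noncentral t distribution gives 106, as stated.
- Allowing for loss: 106/(1 − 0.20) = 132.5, rounded up to 133, as stated.

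The step from SD to n is therefore sound.

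**2. The SD does not reproduce from its formula.** 15 × √(1 − 0.85) = 15 × √0.15 = 5.81, not 11.26. Lost brackets do not explain the gap: with the root over the 1 only, 15 × √1 − 0.85 = 14.15. Other routes from 15 and 0.85 also miss:
- 15 × √0.85 = 13.83
- √2 × SEM = 8.22
- 1.96 × SEM = 11.39
- 15 × √(1 − 0.85²) = 7.90

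**3. One route does match.** 4.36/√0.15 = 11.257, which rounds to 11.26. This is the relation SEM = SD × √(1 − r), solved for SD with 4.36 in the place of the SEM. If that is what was done, the standardised difference is 4.36/11.257 = √0.15 = 0.387. The required n is then 2 × (1.96 + 0.84)²/0.15 ≈ 105 (106 by the t calculation), so it is set by the reliability coefficient.

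**4. What depends on the SD.** Two-sided 5%, Δ = 4.36, t-based; 36 per group is 45 × 0.80:

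| SD | Status | n per group for 80% power | After 20% loss | Power at 45 | Power at 36 |
|---|---|---|---|---|---|
| 11.26 | as stated | 106 | 133 | 44% | 37% |
| 15 | assumption: the unsourced number in the formula's SD position | 187 | 234 | 28% | 23% |

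**The case against.** The strongest reply is that 11.26 may be a reasonable SD behind a misprinted formula. Solving the SEM relation for SD is a legitimate indirect estimate of the between-child SD if 4.36 is itself an SEM and 0.85 is the reliability in a comparable population. The source cited for 4.36 might have used an SEM-based minimum difference, and then only the display would be wrong. This stands as a possibility. It does not remove the point, because the article calls 4.36 a minimum clinically significant difference, never an SEM, and says that the SD came from a formula that does not give it.

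For the same reason, some stronger readings are not supported. A reader might infer that the SD certainly was back-solved from the target difference, that the calculation is circular, or that it rests on no estimate of between-child variability at all. The numerical match is strong, but it remains an inference, and whether the route would be circular depends on what 4.36 is, which the article does not settle. A reader might also conclude that the inputs allow anything from 29 to 187 per group. The 29 takes 5.81 as the SD, although it is an SEM and cannot serve as one. The 187 takes the 15 as an observed SD, which nothing in the article shows.

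It is also fair to say that conduct is unaffected. The 90 is fixed by budget, the article calls the study a pilot, and it discloses reduced power. Under either SD in the table the trial is well short of 80%.

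**Conclusion.** The point holds in this form. The planning SD is wrong as described: the stated formula gives 5.81, not 11.26, and an SEM is not the quantity needed. The value matches 4.36/√0.15, which would be a valid derivation only under an assumption that the article does not state. No sourced between-child SD is documented. The 106 and 133 per group are correct consequences of 4.36 and 11.26, so the error is confined to the origin of the SD.

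The consequence falls on the stated requirement and the implied shortfall in power, not on enrolment or analysis. On the article's own SD, power for its own minimum important difference is 44% at 45 per group and 37% at 36. If the between-child SD were 15, it would be 28% and 23%, with 187 per group required. These figures assume a two-sided 5% t-test with equal variances. The SD of 15 is purely illustrative.

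**What to change.** Rewrite the SD sentence under Sample size calculation:

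- Remove or correct the SEM formula.
- State the between-child SD of the PedsQL score used as outcome, with its source. Alternatively, say explicitly that 11.26 was derived as 4.36/√0.15, and on what grounds 4.36 is taken as an SEM and 0.85 as the reliability in a comparable population.
- If no observed SD is available, show the required size and the power at 45 and 36 per group for SD 11.26 and, labelled as an assumption, SD 15, as in the table above.
- Restate 106 and 133 if the sourced SD differs from 11.26.

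The cost is one paragraph. Enrolment of 90 need not change. The only downside is that the stated requirement and the shortfall may look less favourable.

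### The stated requirement of 160 contradicts the plan's own calculation (212, or 266 with drop-out), and 90 participants give only about 37–44% power for its own clinically important difference

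*Protocol article*

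**What the plan says.** All figures are in the protocol article, under Sample size calculation unless another section is named.

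- Design inputs: "considering a confidence level of 95%, a power of 80%, equal variances between groups, and a 1:1 ratio between sample sizes".
- Target: "The difference in means to be detected was set at 4.36, based on literature identifying this value as the minimum clinically significant difference".
- SD: "The common standard deviation was calculated at 11.26, using the formula for the standard error of measurement".
- Result: "resulting in a required sample size of 106 participants per group". For an estimated 20% loss, "the sample size was increased to 133 participants per group".
- The budget then fixes the sample at 90 in total, about 45 per group. The paragraph comments: "While this is lower than the 160 participants initially estimated through power calculations". It gives no source for 160 and does not state the power at 90. It ends by repositioning the study as a pilot randomized trial meant to produce preliminary data.
- The Limitations section describes the consequence of the shortfall as "potentially reducing the statistical power to detect small effect sizes".
- The Statistical analysis section answers the primary question with an independent-samples comparison of intervention and control at p < 0.05.

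**The concern.** The paragraph credits the power calculation with two different results. The sentence containing 160 is the one that tells the reader how far the trial falls short, and the number it uses makes the shortfall look much smaller than it is.

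The consequence of the shortfall is also understated. The only power figure in the document is 80%, which belongs to a design that will not be run. A reader of the Limitations section would conclude that the trial may miss minor effects but can still find effects that matter. If the power is in fact low for the plan's own clinically important difference, a non-significant result would say little about whether the programme works. The designers of the larger trials that this study is meant to inform could also carry 160 forward as the calculated requirement.

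**Working it through.** **Inputs from the protocol article.** Difference δ = 4.36; SD σ = 11.26; power 80%; confidence 95%; ratio 1:1; loss 20%; final sample 90 (45 per group). The article does not say whether the test is two-sided. Two-sided 5% is taken here because it reproduces 106; a one-sided 5% test gives 83 to 84 per group.

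**1. Reproduce the plan's figures.**
- Standardised difference: 4.36 / 11.26 = 0.387.
- Normal approximation: n = 2 × [σ(1.96 + 0.8416)/δ]² = 104.7, so 105 per group.
- t-based calculation: 105.67, so **106 per group**, as stated. Total 2 × 106 = **212**.
- Loss: 106 / (1 − 0.20) = 132.5, so **133 per group**, as stated. Total 2 × 133 = **266**.

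**2. Look for a route to 160.** With δ and σ held at the plan's values, one- and two-sided tests, alpha of 0.05 and 0.10, and power from 70% to 90% were tried, with and without inflation for loss. None gives a total of 160. The nearest is 166 (83 per group: for example one-sided 5%, 80% power, no loss), which contradicts the stated 106. A standardised difference of 0.5 would give 64 per group, and 2 × 64 / 0.8 = 160, but the plan's ratio is 0.387. This is only a possible origin.

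**3. Size of the shortfall.**
- Against 160: 90 / 160 = 56%.
- Against 212: 90 / 212 = 42%.
- Against 266: 90 / 266 = 34%.

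**4. What 90 participants give**, with σ = 11.26, a two-sided 5% t-test and no baseline adjustment. The 36 per group is 45 × 0.8, the plan's own loss rate. The last row shows what 160 would have given.

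| Analysed per group | Power for 4.36 | Difference detectable with 80% power | 95% CI half-width |
|---|---|---|---|
| 45 | 44.3% | 0.597 × 11.26 = 6.72 | 1.987 × 11.26 × √(2/45) = 4.72 |
| 36 | 36.7% | 0.670 × 11.26 = 7.54 | 1.994 × 11.26 × √(2/36) = 5.29 |
| 80 (160 in total) | 68.2% | 5.02 | 3.52 |

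The normal approximation gives 45.1% and 37.6% in the first two rows. The detectable differences are 6.72 / 4.36 = 1.5 and 7.54 / 4.36 = 1.7 times the stated important difference. Even 160 participants would not have reached 80% power on these inputs.

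**5. Dependence on the SD.** The printed formula gives 15 × √(1 − 0.85) = 5.81, not 11.26. The value 11.26 equals 4.36 / √0.15, so the difference seems to have been put in the place of the standard error of measurement. Power for 4.36 at 45 and 36 per group is:
- SD 5.81: 94% and 88%. This value is a standard error of measurement, not a between-patient SD.
- SD 11.26: 44% and 37%.
- SD 15, if the 15 in the formula is the SD: 28% and 23%.

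**The case against.** The best defence is that the shortfall is disclosed. The sample size section gives the budget as the reason and relabels the study a pilot, the Discussion repeats that the sample is smaller than calculated, and Limitations lists it first. The correct 106 and 133 per group stand just before 160, and no allocation or analysis rule uses 160. Being called an initial estimate, it may be left over from an earlier calculation. A standardised difference of 0.387 is below the usual benchmark of 0.5 for a medium effect, so calling it small can be defended: with 45 per group, power is 65% for 0.5 and 96% for 0.8. Finally, every power figure above rests on an SD that the printed formula does not support.

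The last point stands in part: any power printed in the protocol must be labelled as conditional on the SD. The contradiction between 160 and 212 or 266 does not depend on the SD at all.

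The rest does not remove the problem. Disclosing a shortfall does not make its stated size right, and a pilot label does not tell the reader how to take a null result when the primary question is still tested at p < 0.05. Whatever the benchmark, the plan itself calls 4.36 the minimum clinically significant difference, so describing the lost power as power for small effects hides that the important effect is among those lost.

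**Conclusion.** The concern holds on both parts.

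1. The figure of 160 is wrong as written. The calculation described supports 212 in total, or 266 with 20% loss. The trial therefore has 34% of its calculated size, where the text implies 56%.
2. At 90 participants the power for the plan's own clinically important difference is about 44% with no loss and 37% with the planned loss. On these inputs, a non-significant result is more likely than a significant one even if the programme truly delivers 4.36 points. The Limitations wording understates this.

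The second part assumes the stated SD of 11.26, a two-sided 5% t-test, no baseline adjustment and the plan's 20% loss applied to 90. A between-patient SD of 15 would lower the power to 23–28%. The first part needs none of these assumptions. It should be corrected before the document is relied on, because it misstates the headline sample size.

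**What to change.** - **Sample size calculation:** replace 160 with 266 (133 per group), or with the recomputed total once the SD has been settled. If 160 came from a separate calculation, give its inputs and reconcile it with 106 and 133 per group.
- **Same section:** add the operating characteristics of the design to be run. With an SD of 11.26 and a two-sided 5% test, 90 randomised participants give about 37–44% power for 4.36, a difference detectable with 80% power of 6.7–7.5 points, and a 95% CI half-width of about 5 points (4.7–5.3). Label these as conditional on that SD and recompute them if it changes.
- **Limitations:** say that the trial is not powered for its own minimum clinically significant difference, and that a non-significant result will not rule that difference out.

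The cost is text only. No extra patients and no design change are needed; the stated power becomes less favourable.
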